## Abstract

**Background:**

Irritable bowel syndrome (IBS) is a chronic gastrointestinal disorder characterized by abdominal pain and change of bowel habit without organic disease. A global perspective given by the World Gastroenterology Organization (WGO) points out that IBS can impact the quality of an individual’s daily life, cause socioeconomic problems and potentially impair the patient-physician relationship. It remains a problem to treat IBS due to the complicated pathophysiology. Acupuncture is an alternative therapy recommended for IBS. The aim of this study is to investigate the efficacy and safety of acupuncture therapy for patients with IBS. We also want to explore the correlation between IBS-gene subtypes and acupuncture effect.

**Methods/design:**

A multicenter randomized controlled trial will be performed in seven hospitals. Six hundred participants will be stratified into two strata (IBS-C or IBS-D). Then, patients within each stratum will be divided into an experimental group and a control group randomly. The experimental group is treated with acupuncture while the control group is treated with Western medicine. All the patients will receive a 6-week treatment and a 3-month follow-up. The primary outcome is the IBS-Symptom Severity Score (IBS-SSS), the secondary outcome is the score of the IBS-Quality of Life (IBS-QoL).The correlation between IBS-gene subtypes and acupuncture effect will be detected based on polymerase chain reaction-restriction fragment length polymorphism (PCR-RFLP). Outcome measures (including primary and secondary outcome measures) are collected at baseline,1 week, 2 weeks, 4 weeks, and 6 weeks of the intervention, and 12 weeks after the intervention.

**Discussion:**

This is a multicenter randomized controlled trial for IBS in China. It may clarify the efficacy of acupuncture as an alternative therapy for IBS. This is the first time ever that the potential mechanism of IBS based on genomics has been investigated.

**Trial registration:**

Chinese Clinical Trials Register, ID: ChiCTR-IOR-15006259. First registered on 14 April 2015.

**Electronic supplementary material:**

The online version of this article (10.1186/s13063-018-2922-y) contains supplementary material, which is available to authorized users.

## Background

Irritable bowel syndrome (IBS) is the most common functional gastrointestinal disorder, yet it is also one of the least well-understood medical conditions. Epidemiological data shows that the prevalence of IBS is approximately 11% in the world [1] and 5–6% in China [2]. The main clinical feature of IBS is abdominal pain related to defecation or a change in stool form and/or frequency at least once a week in the preceding month [3, 4]. Although IBS is not a life-threatening disorder, it significantly reduces the patient’s quality of life and imposes a considerable economic burden on individuals, families, and society, with decreased work productivity and increased healthcare spending and utilization [5, 6].

Abnormalities in the brain-gut interaction and gastrointestinal mobility, and visceral hypersensitivity are the main pathophysiological basis of IBS, but their underlying mechanisms have not been fully elucidated. IBS is also associated with various psychosocial and environmental factors, including early life stress, food intolerance, antibiotic abuse, and intestinal infections. In addition, family and twin aggregate studies have suggested the role of genetic factors in the pathogenesis of IBS [7, 8]. In particular, polymorphisms in the serotonin reuptake transporter (*SERT*) gene have been widely implicated in the disturbances of gastrointestinal functions in IBS. The *SERT* gene is responsible for controlling the synaptic concentration of serotonin, or 5-hydroxytryptamine (5-HT), which is an important neurotransmitter and paracrine signaling molecule involved in the brain-gut axis and regulation of gastrointestinal mobility and sensation. So, modifications in the *SERT* gene affect the intensity and duration of serotonergic signaling. Recent studies have identified several polymorphisms in the serotonin-related genes associated with IBS, including the 5-HT-transporter-gene-linked polymorphic region (*5-HTTLPR*), variable number of tandem repeats *STin2*, and the single-nucleotide polymorphism (SNP) *rs25531* [9–12].

Despite these findings and advances in IBS research, the pathophysiology of IBS is still poorly understood with no definitive biomarker, thereby hampering the development of effective therapies for IBS [13]. Currently available treatments for IBS can be broadly classified into pharmacological therapies and other interventions, such as dietary and lifestyle modifications [6, 14]. There are various pharmacological treatments for IBS, including 5-HT-receptor modulating agents, antispasmodics, probiotics, and antidiarrheal agents [15]. While some have been found to be effective, they are not uniformly effective across all patients. There are also potential risks of adverse effects and substantial financial burden associated with the use of pharmacological treatments [6, 16].

As a result of dissatisfaction with the effectiveness, safety, and costs of pharmacological treatments, there has been a rise in the use of non-pharmacological therapies, including acupuncture [17]. Acupuncture is an important modality of traditional Chinese medicine (TCM), which involves an insertion of a needle into the body at specific points to prevent and treat various diseases. It has a long history originating in ancient China and has been used for thousands of years to treat digestive problems. In recent research, there has been a growing interest in investigating the possible role of acupuncture in improving symptoms and quality of life in IBS patients [18]. Current evidence suggests that acupuncture is more effective than pharmacological therapies [19]. However, there are still limitations with current research, including small sample sizes and lack of detailed assessment of improvement and side effects [20]. In addition, the role of genetic polymorphisms in the treatment of IBS with acupuncture has not yet been studied. In 2014, our team conducted a meta analysis of IBS research in seven countries, and showed that there was a correlation between the 5-HTTLPR gene polymorphism and the incidence of IBS-D and IBS-C [21, 22]. As a result, large-scale, methodologically rigorous studies are needed to assess the effectiveness and safety of acupuncture for IBS as well as investigate the role of genetics in IBS.

## Methods/design

The protocol for this trial is reported based on the Standard Protocol Items: Recommendations for Interventional Trials (SPIRIT) 2013 Checklist: defining standard protocol items for clinical trials (Additional file 1). The study has been approved by the Ethics Committee of Jiangsu Province Hospital of TCM (the Approved No. of the Ethics Committee is 2015NL-030-02) and was registered on at the Chinese Clinical Trial Registry (Chictr) platform on 14 April 2015 (Registration number: ChiCTR-IOR-15006259).

### Study design

This study is a multicenter, stratified randomized controlled trial (RCT), comparing acupuncture to standard pharmacological treatment for two subtypes of IBS: IBS-C (constipation-predominant IBS) and IBS-D (diarrhea-predominant IBS). The study is being conducted in the following seven hospitals: Jiangsu Hospital of TCM, Wuxi Hospital of TCM, Nantong Hospital of TCM, Nanjing Hospital of Chinese Medicine, Zhenjiang Riverside Hospital, Kunshan Hospital of TCM, and Shuyang Hospital of TCM. The study will be carried out according to the principles of the Declaration of Helsinki (version Edinburgh 2000).

This study will be performed over a period of 19 weeks: 1 week of wash-out, 6 weeks of treatment, and 12 weeks of post-treatment follow-up. All eligible patients will be stratified into two strata: IBS-C or IBS-D. The patients within each stratum will then randomly divided to either an acupuncture group or a control group receiving standard pharmacological treatment. Outcomes will be assessed at baseline, during the treatment and at the end of the follow-up. Figures 1 and 2 illustrate the time schedule of enrollment, interventions, assessments, and participant visits.

**Fig. 1 Fig1:**
[figure not shown]
Trial flow chart

**Fig. 2 Fig2:**
[figure not shown]
Standard Protocol Items: Recommendations for Interventional Trials (SPIRIT) Schedule for enrollment, interventions, and assessments

### Randomization and blinding

The Good Clinical Practice (GCP) Center of Jiangsu Province Hospital of TCM will be responsible for generating the randomization sequence. All eligible participants will be told not to take any treatment for IBS for 1 week (the wash-out period). After the wash-out period, all the participants will be stratified into IBS-C or IBS-D subgroups and then randomly allocated to either the acupuncture group or the control group by a central randomization system. An allocation ratio of 2:1 will be used in the acupuncture to control group assignment. Only the outcome assessors and the statisticians will be blinded to the allocation. The outcome assessors and the statisticians will not participant in the treatment, they will perform the outcome evaluation and the statistical analysis independently.

### Study participants and the recruitment

Participants will be recruited from the outpatient centers of the seven participating hospitals and their surrounding communities by posting and distributing posters and flyers about this trial.

The following inclusion criteria will be used: (1) adults aged 18–70 years, (2) diagnosis of IBS-C or IBS-D, as defined by ROME III diagnostic criteria [4], (3) IBS duration of 6 months or longer, (4) lack of morphological changes and biochemical abnormalities that could explain the symptoms, (5) baseline IBS-Symptom Severity Score (IBS-SSS) score of 75 points or greater, (6) no acupuncture treatment for 3 months preceding the trial, (7) no participation in any other ongoing clinical trial, and (8) agreement to participate and signing of the informed consent document.

The exclusion criteria are: (1) diagnosis of an organic intestinal disease, (2) history of abdominal and/or rectal surgery, (3) history of drug dependence for gastrointestinal motility and function, (4) other serious medical conditions, such as cardiovascular disease, endocrine disorders, hepatic dysfunction, cerebral vascular disease, renal diseases, and cognitive disorders, and (5) pregnancy, lactation, and postpartum period of less than 12 months. Physical examination will be conducted at the time of recruitment to exclude participants with serious diseases not suitable for this trial.

### Acupuncture and the control group

Patients in the acupuncture group, regardless of the IBS subtypes, will receive acupuncture three times a week for 6 weeks for a total of 18 treatment sessions. Patients will receive treatment in supine position for 30 min per session. The treatment will be provided by licensed acupuncturists holding acupuncture physician certifications in China with at least 2 years of clinical experience. Disposable, sterile needles with a diameter of 0.30 mm and a body length of 40 mm (Huatuo, Suzhou, China) will be used. Based on TCM theory and our clinical experience, acupoints used here are unilateral *GV20* (*Bai Hui*), *GV29* (*Yin Tang*) and bilateral *LR3* (*Tai Chong*), *ST36* (*Zu San Li*), *SP6* (*San Yin Jiao*), *ST25* (*Tian Shu*), and *ST37* (*Shang JuXu*) (Fig. 3). The exact location and depth of needling for each point will be determined based on the 2006 People’s Republic of China National Standard (GB/T 12346–2006) Acu-Points Name and Location [23]. After insertion, all points will be manually stimulated by lifting and thrusting the needle every 10 min to elicit the “*deqi*” and the needles will be retained for 30 min.

**Fig. 3 Fig3:**
[figure not shown]
Locations of acupoints: acupuncture group

The patients in the control group will receive standard pharmacological treatment based on the IBS subtype. Patients with IBS-C will take macrogol 4000 powders (Fu Song, two bags per day, dissolved in a glass of water before taking) for 6 weeks. Patients with IBS-D will take pinaverium bromide tablets (Dicetel, 50 mg tid, swallowing pills with water during meals without breaking, chewing or dissolving) for 6 weeks.

### Outcome assessment

The primary outcome measure of this trial is the IBS-Symptom Severity Score (IBS-SSS), a validated scoring system for assessing the severity of IBS [24, 25]. The questionnaire is scored from 0 to 500 and is composed of five 100-point scales that measure the severity of pain, duration of pain, severity of abdominal distention, dissatisfaction with bowel habits, and disruption in life quality. The scores are classified into no IBS (< 75), mild IBS case (75–175), moderate IBS case (175–300), and severe IBS case (> 300) [25]. IBS-SSS is assessed at baseline, 1, 2, 4, 6, and 18 weeks.

The secondary outcome measures include the IBS-Quality of Life (IBS-QoL) and genotyping of the patients’ serotonin-related genes. The IBS-QoL is a 34-item questionnaire for determining the degree to which IBS interferes with the patient’s quality of life [26]. It is composed of eight dimensions, including dysphoria, interference with activity, body image, health worry, food avoidance, social reaction, sex, and relationships. Each item is evaluated on a 5-point rank scale with a higher score indicating a better quality of life. The IBS-QoL will be measured at baseline and 6 and 18 weeks.

DNA isolation and genotyping will be performed to study the possible correlation between the therapeutic effectiveness of acupuncture and the following polymorphisms of serotonin-related genes: (1) *HTTLPR* (*L/L*, *L/S*, *S/S*), (2) *STin2 VNTR* (*STin2 12/12*, *STin2 12/10*, *STin2 12/9*, *STin2 10/10*, *STin2 9/9*), and (3) *rs25531* (*rs25531-G*). The patients’ blood samples will be collected at the baseline. The correlation between IBS-gene subtypes and acupuncture effect will be detected based on cleaved amplification polymorphism sequence-tagged sites.

### Sample size calculation and statistical analysis

Based on our previous clinical experience and the previous literature, we anticipate an improvement of 115 points in the acupuncture group and 105 points in the control group on the IBS-SSS. The standard deviation is set at 37, and the ratio between the acupuncture and control groups is 2:1. The sample size is calculated with 80% power and 5% type I error using G*Power software (version, Franz Faul, Universitat Kiel, Germany). This resulted in a required sample size of 322 participants in the acupuncture group and 161 participants in the control group. After accounting for a 20% drop-out rate, 400 participants in the acupuncture group and 200 participants in the control will be included.

Statistical analysis of all data in this study will be performed by a specialized statistician, who is blinded to the treatment allocation. Statistical Package for the Social Sciences (SPSS) V.24.0 (SPSS Inc., Chicago, IL, USA) will be used for data analysis. All analysis will be on the basis of the intention-to-treat (ITT) population and the per-protocol (PP) population. ITT requires all participants in a clinical trial to be included in the analysis in the groups to which they were randomized, regardless of any departures from randomized treatment. The PP population is usually defined as all patients completing the study without major protocol deviations – that is those who followed the rules of the study. The results of each population will be compared for stabilization. Last-observation-carried-forward will be used in the case of missing data. The principal investigator will take responsibility for the results of the data analysis. In terms of data description, quantitative and qualitative data will be presented as mean ± standard deviation, frequency, percentages or constituent ratios, respectively. Other covariates such as age, gender, ethnicity, disease duration, marital status, educational level, weight (in kilograms), and height (in meters) will be considered for further revision. In case of normality of distribution and homoscedasticity, the baseline characteristics will be performed using the analysis of covariance (ANCOVA) model, and the multiple comparisons will be performed with the Least Significant Difference test. In addition, a repeated- measure analysis of variance (rm-ANOVA) will be used to determine, within each group, the difference between baseline and 1, 2, 4, 6, and 18 weeks for both the IBS-SSS and the IBS-QoL. On this occasion of non-normal distribution data and heteroscedasticity data, the non-parametric Kruskal-Wallis test will be performed, and the Nemenyi test will be done to identify the difference between the groups. Pearson’s chi-squared test will be used in the transformed categorical data. Lastly, we will conduct rm-ANOVA to analyze genotype-related effects on treatment response. The Huynh-Feldt correction will be used if the assumption of sphericity is violated. A two-sided *p* value of less than 0.05 will be considered statistically significant for all analyses.

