Nevertheless, there are still limitations in this study that should be noted. First, the main outcome measures are subjective evaluation scales which lack objective evidence to support the effect of a given treatment directly. Second, after completion of the 6-week treatment, a 3-month follow-up will be conducted, the drop-out rate may be higher. In order to minimize potential drop out, we have established guidelines and training for research staff to establish good communication relationships with the participants.

In conclusion, the results of this methodologically rigorous trial are expected to not only provide clinical evidence of the effectiveness and safety of acupuncture in treating IBS, but also investigate the role of genetics in IBS.

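### LOCF is the only missing-data method: a mild dilution if drop-out is alike in both arms, but a bias of several points on a 10-point target if its rate or timing differs by arm

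*Protocol article*

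**What the plan says.** The statistical section of the Protocol article sets one rule for missing data: "Last-observation-carried-forward will be used in the case of missing data". It is not limited to an outcome, a visit or a population.

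The same section gives the planning figures. It puts the expected gains this way: "we anticipate an improvement of 115 points in the acupuncture group and 105 points in the control group on the IBS-SSS". It takes an SD of 37 and two acupuncture patients for each control patient. Its allowance for losses reads: "After accounting for a 20% drop-out rate, 400 participants in the acupuncture group and 200 participants in the control will be included". The 20% is not split by arm or by time.

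Outcome assessment schedules IBS-SSS at baseline and at weeks 1, 2, 4, 6 and 18. Treatment lasts six weeks, so the last visit falls 12 weeks after it ends. The Discussion adds that "a 3-month follow-up will be conducted, the drop-out rate may be higher" and describes staff guidelines and training meant to limit this.

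The only robustness check is a comparison of the ITT and per-protocol results.

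**The concern.** The expected change within each arm is more than ten times the expected difference between arms. A rule that fixes leavers at a partial improvement can therefore move the arm difference by an amount comparable with the target, if the arms lose different numbers of patients or lose them at different times.

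LOCF does three things here:

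- A patient who leaves at week 1 or 2 keeps that early score at weeks 6 and 18.
- A patient lost after week 6 is scored at week 18 as if nothing had changed during 12 weeks off treatment.
- Every carried-forward score counts as an observation.

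Unequal drop-out is plausible. Patients know their allocation, and the arms differ in burden: 18 clinic sessions against self-taken drugs. Comparing ITT with per-protocol does not test the LOCF assumption, because the per-protocol set is built from completers.

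**Working it through.** **The plan's own figure.** Inputs are a difference of 10, SD 37, 2:1 allocation, 80% power and two-sided 5%. Control n = (1.960 + 0.842)² × 37² × (1 + 1/2) / 10² = 161.2, so 162 control and 324 acupuncture after rounding up. The article's "required sample size of 322 participants in the acupuncture group and 161 participants in the control group" reproduces (power about 0.80). Dividing by 0.8 gives 403 and 202, against 400 and 200 planned. The sample size is not in question; it supplies the inputs below.

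**Bias at week 6.** The article does not say to which visit the 115 and 105 refer; end of treatment is assumed. Let d be the drop-out proportion before week 6 and s the share of the arm's mean improvement still missing when a leaver was last seen. Assume leavers would have reached the arm mean had they stayed. LOCF then turns an arm mean μ into μ(1 − d·s), so

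bias in the difference (acupuncture − control) = 105·d_C·s_C − 115·d_A·s_A.

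*Same rate and timing, 20% in both arms:* 0.20 × (105 − 115) × s = −2.0·s. For s from 0.25 to 1 the bias is −0.5 to −2.0, so 10 points become 9.5 to 8.0. If the true means are equal, the bias is zero.

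*Different rates, same s.* The splits are assumptions; with 2:1 allocation they pool to about 18% and 22%, near the planned 20%.

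| Drop-out, acupuncture / control | Bias | s = 0.3 | s = 0.7 |
|---|---|---|---|
| 15% / 25% | (26.25 − 17.25)·s = +9.0·s | +2.7 | +6.3 |
| 25% / 15% | (15.75 − 28.75)·s = −13.0·s | −3.9 | −9.1 |

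The two directions are not mirror images because the arm means differ.

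*Same 20% rate, different timing:* with s = 0.25 on acupuncture and 0.75 on control, 0.20 × (78.75 − 28.75) = +10.0. Reversed, 0.20 × (26.25 − 86.25) = −12.0.

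*Loss after week 6:* these patients have a week-6 score, unless that visit was missed, and add no bias there. If half of the drop-out came after week 6, the table's ranges would halve to about 1.4 to 3.2 and 2.0 to 4.6.

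**False positives.** Suppose both arms truly improve by 105 and drop-out is 15% / 25%. The spurious difference is 0.10 × 105 × s = 3.15 (s = 0.3) to 7.35 (s = 0.7). Mixing leavers with stayers adds d(1 − d)(105·s)² to each arm's variance of 37². With 400 and 200 patients the standard error is then 3.39 to 4.13, and a two-sided 5% test rejects in about 15% to 43% of trials. This takes SD 37 for leavers and stayers alike.

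**Week 18.** For patients lost after week 6, let R be the points of improvement that would have been lost by week 18. Each arm's mean is overstated by d·R, and the difference is biased by d_A·R_A − d_C·R_C. The documents give no R, so these values are illustrative:

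- 20% loss and R = 50 in both arms: each mean is overstated by 10 points and the difference by 0.
- 15% / 25% loss with R = 50 in both: 7.5 − 12.5 = −5.0.
- 20% loss in both, R = 60 on acupuncture and 20 on control: 12 − 4 = +8.0.

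**Imputed values counted as data.** With SD 37 the standard error is 3.20 at 400 + 200 and 3.58 at the 320 + 160 left after 20% loss. LOCF takes the larger count as observed. Because it also adds variance, as above, the net error in the standard error cannot be fixed from the documents.

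**The case against.** The strongest reply is that every large figure above depends on drop-out rate, timing or relapse differing between arms, and the article reports none of these. Its 20% is a single planning figure, and staff are trained to keep patients in the trial. That stands. A reader might infer that 20% drop-out is in itself enough for LOCF to create or hide most of the 10-point target. The documents do not support this: with like drop-out in both arms the loss is at most 2 points, and no false difference arises.

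A reader might also infer that week-18 durability will be overstated. The article says nothing on relapse; scores could be stable or still improving. The statement holds only if symptoms return.

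Two further limits stand. The Discussion's warning concerns the follow-up period, so it supports the week-18 concern rather than the week-6 figures. And patients who leave for lack of effect might never have reached the arm mean, in which case the bias is smaller than shown.

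None of this justifies LOCF. The article itself fixes the method, so this is not a detail left to an unseen analysis plan. The plan relies on an equality between arms that it neither states nor checks.

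**Conclusion.** The point holds in conditional form. As the sole missing-data method, LOCF is a poor choice for this trial. Its effect is a dilution of 0.5 to 2.0 of the 10 points if drop-out is alike in both arms. Under a 10-percentage-point imbalance it is 2.7 to 6.3 points towards acupuncture or 3.9 to 9.1 against it. The direction cannot be known in advance. These ranges rest on assumed splits of 15% / 25% and 25% / 15%, on 30% to 70% of the improvement being missed, on leavers otherwise reaching the arm mean, and on all loss falling before week 6. Confidence is high that the method is unsuitable and lower on the size of the bias. The plan should be changed, though the finding does not show that the trial's result will be wrong.

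**What to change.** For the between-arm comparison of IBS-SSS, replace LOCF with a mixed model for repeated measures fitted to all observed visits. Include treatment, visit, treatment-by-visit, baseline-by-visit and IBS subtype, and estimate the arm difference at each visit from the model. The MIXED procedure in the SPSS software already named can fit it.

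Add a delta-adjusted or control-based multiple-imputation sensitivity analysis for week 18. Keep LOCF at most as a further sensitivity analysis, and report drop-out by arm and by last visit attended. The within-group repeated-measures ANOVA and its sphericity correction are a separate matter and need not change on account of this point.

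The cost is a change of wording and some extra programming, with no new data. The mixed model relies on data being missing at random, which the sensitivity analysis is there to examine. The article reports 540 participants recruited and the trial ongoing, so the change should be dated and made while the statistician is still blinded.

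### No planned analysis names the baseline IBS-SSS or IBS-QoL score as a covariate, so precision available from data already collected is left unused

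*Protocol article*

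**What the plan says.** Under Outcome assessment, the primary outcome is scheduled as follows: "IBS-SSS is assessed at baseline, 1, 2, 4, 6, and 18 weeks". IBS-QoL also has a baseline measurement. Baseline IBS-SSS is an entry criterion as well (75 points or more, under Study participants and the recruitment).

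Under Sample size calculation and statistical analysis, the trial is sized on change: "we anticipate an improvement of 115 points in the acupuncture group and 105 points in the control group on the IBS-SSS", and "The standard deviation is set at 37". No covariate adjustment enters that calculation.

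The analysis text in the same section has three parts that bear on the point:

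- **Covariates.** The text reads "Other covariates such as age, gender, ethnicity, disease duration, marital status, educational level, weight (in kilograms), and height (in meters) will be considered", leaving their use to be settled later. Neither baseline score is listed.
- **ANCOVA.** It is named once, with the baseline characteristics as its object. Neither its outcome nor its covariate is stated.
- **Repeated-measures ANOVA.** It is applied within each group, to "the difference between baseline and 1, 2, 4, 6, and 18 weeks for both the IBS-SSS and the IBS-QoL". Here baseline is one level of time.

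**The concern.** The baseline value of an outcome is commonly among the best predictors of its later value. The scale gives a reason to expect that here. Entry opens at 75 points and the score cannot fall below 0, so a patient who enters at 75 to 104 cannot improve by as much as either anticipated mean (115 or 105). How far a patient can improve therefore depends on where that patient starts.

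The target difference is only 10 points, so the standard error matters. Randomisation is stratified by IBS subtype and not by severity, so the design does not hold starting severity level between the 2:1 arms. A comparison of change without adjustment absorbs a chance imbalance into the estimate for the trial at hand. Adjusting for the baseline score removes it in expectation and shrinks the residual variance. The analysis text names variables such as marital status and height for possible adjustment but leaves this one out.

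**Working it through.** **Inputs from the article.** Difference 115 − 105 = 10; SD 37; "the ratio between the acupuncture and control groups is 2:1"; "The sample size is calculated with 80% power and 5% type I error"; two-sided testing at 0.05; 322 + 161 required; 20% drop-out; 400 + 200 enrolled.

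**Reproducing the stated size.** For 2:1 allocation without adjustment, the control-arm size is

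n = 1.5 × [37 × (1.960 + 0.842) / 10]² = 161.2

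This agrees with the stated 161 (and 322) up to rounding. Power at 322/161 by noncentral t is 79.8%. The plan is therefore sized as an unadjusted two-sided comparison of mean improvement, and it delivers what it states.

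**Effect of adjustment.** Take 37 as the SD of change, ρ as the correlation between baseline and follow-up score, and equal SDs at the two visits. Then

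- residual SD under ANCOVA = 37 × √((1 + ρ)/2)
- implied baseline SD = 37 / √(2(1 − ρ))

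After 20% drop-out, 320 and 160 remain. The unadjusted standard error is 37 × √(1/320 + 1/160) = 3.58 and power is 79.6%.

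| ρ (assumed) | Implied baseline SD | Residual SD | SE | Power | Gain (points) |
|---|---|---|---|---|---|
| 0.3 | 31 | 29.8 | 2.89 | 93.3% | 13.7 |
| 0.5 | 37 | 32.0 | 3.10 | 89.6% | 10.0 |
| 0.7 | 48 | 34.1 | 3.30 | 85.6% | 6.0 |
| 0.8 | 59 | 35.1 | 3.40 | 83.6% | 4.0 |
| 0.9 | 83 | 36.1 | 3.49 | 81.5% | 2.0 |

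**Reading by baseline SD.** The article gives no baseline SD. With the SD of change held at 37, ρ = 1 − 37²/(2 × SD²). A baseline SD of 60 gives ρ = 0.81 and a gain of 3.8 points; 70 gives 0.86 and 2.8; 80 gives 0.89 and 2.1.

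**All 600 analysed.** The plan specifies intention-to-treat with last observation carried forward, so up to 400 and 200 may enter. At ρ = 0.5, power then goes from 87.6% to 94.9%, a gain of 7.3 points. This treats carried-forward values as having the same SD and correlation as observed ones.

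**If 37 is a single-visit SD.** The article does not label the SD. On that reading the residual SD is 37 × √(1 − ρ²), which at ρ = 0.5 is again 32.0, so the result at 0.5 does not depend on the reading.

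**Chance imbalance.** At ρ = 0.5 the baseline SD is 37, so a one-standard-error imbalance at baseline is 3.58 points. It shifts the unadjusted change estimate by (1 − 0.5) × 3.58 = 1.8 points, or 18% of the 10-point target.

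**The case against.** There are four serious counter-arguments.

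**The covariate list is open.** It begins with *other* and *such as*, and the ANCOVA sentence beside it is garbled enough that a baseline-adjusted ANCOVA may have been meant. This stands. A reader might infer that the plan excludes baseline adjustment; the text does not support that. Adjustment is unnamed, not ruled out.

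**An article may leave covariates to the full protocol or analysis plan.** This has force, and silence alone would be no finding. But the article does not stay silent. It names eight covariates and the models, and its Trial status section gives unspecific statistical methods as one reason for revising the protocol. A covariate set has been put forward, and it lacks the baseline score.

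**No between-arm change-score test is written down.** This is correct. The repeated-measures ANOVA is within group, and the between-arm comparison of change is inferred from the sample-size inputs. The point is best settled together with stating that between-arm model.

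**Nothing promised is lost.** A reader might infer that the trial is underpowered or its estimate biased. Neither follows. The size reproduces at about 80% without adjustment. Under randomisation the unadjusted comparison of change is unbiased: regression to the mean acts on both arms alike in expectation, and chance imbalance is already reflected in the standard error. A flat claim of a 10-point cost in power would also be too firm. It needs ρ = 0.5, hence a baseline SD of only 37, although entry runs from mild to severe disease on a 0 to 500 scale. A wider baseline spread makes the gain smaller.

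**Conclusion.** The point holds as one of forgone precision. The analysis section does not name the baseline score as a covariate for either outcome, although both are measured at baseline in all patients. The trial still has its planned power and an unbiased comparison.

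With 320 and 160 analysed, the gain forgone runs from about 14 points of power at ρ = 0.3 to about 2 at ρ = 0.9. For baseline SDs of 60 to 80 it is about 4 to 2 points. These figures rest on 37 being the SD of change, equal SDs at both visits and an assumed ρ. The direction does not depend on ρ: under equal SDs, the residual variance is (1 + ρ)/2 of the change-score variance, which is below 1 for every ρ below 1. Only the size is uncertain. The change is worth making because it is nearly free, and because 540 of 600 participants were already recruited when the article was written, so little precision can still come from enrolment.

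**What to change.** In Sample size calculation and statistical analysis, state that the between-arm comparison of IBS-SSS uses ANCOVA, or a repeated-measures model with the post-baseline scores as outcome. Make baseline IBS-SSS a prespecified continuous covariate; in the repeated-measures model, add a baseline-by-visit term. The baseline is then neither the first time level nor merely a value to subtract. Do the same for IBS-QoL with its own baseline score. List these as fixed covariates, ahead of those that are only to be considered.

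Keep the stated sample size. The cost is a sentence or two before database lock and one degree of freedom, or one per visit with the interaction, which is negligible with 480 or more patients. No new data, patients or staff are needed.
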